### Interventions, administration and duration

As part of the trial design, all enrolled patients will receive intervention following embolization of the aneurysm. The UFH group will start intravenous infusion of UFH 24 h after the embolization procedure, upon confirmation of inactive bleeding through head CT scan. The heparin will be administered at a dose of 8–10 U/kg/h, and APTT values will be monitored twice a day for 7 consecutive days. The infusion rate of heparin will be adjusted based on APTT values to maintain it within the range of 35–45 s. In case of APTT values exceeding or falling below the set range, the infusion rate will be decreased or increased by 1 IU and maintained for 12 h. As per FDA standards for the use of low molecular weight heparin, the UFH group will receive subcutaneous injection of prophylactic dose of LMWH (4000 IU) every 12 h for a duration of 1 week starting 24 h after the aneurysm repair.

All experimental UFH is stored in original packaging at 15–30 °C (protected from light and heat). LMWH is stored at 2–8 °C. After opening for more than 24 h, heparin should be discarded. During the administration process, the nursing staff is trained on medication usage and provided with dosing instructions and adverse reaction management plans for both the UFH and LMWH group. To ensure blinding, any communication between the research staff and participants that may reveal group allocation should be avoided. The identity of the medication provider should also not be disclosed.

During hospitalization, both groups of patients will be closely monitored for vital signs and symptoms in the intensive care unit. Platelet-inhibiting agents, nonsteroidal anti-inflammatory drugs, and oral anticoagulants are prohibited during the patient’s treatment period. Physicians will check for interactions with heparin when using other medications and closely monitor bleeding symptoms, adjusting the dosage of heparin or other medications as needed. All patients will receive oral nimodipine, and the blood volume will be maintained in equilibrium. The intracranial pressure of all patients will be monitored with the transducer. Transcranial Doppler (TCD) ultrasound will be performed daily to evaluate for CV, and a weekly follow-up head CT will be performed. In cases where CV or increased intracranial pressure is suspected, urgent head CT angiogram (CTA) or CT scans will be performed for confirmation.

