### Outcome assessments

#### Baseline assessment

Baseline variables encompass demographic information (gender, age, ethnicity, prior medical history, personal life history), comorbidities, vital signs (blood pressure, heart rate, respiratory rate), concomitant medication, surgical intervention (e.g., decompressive craniectomy), and results of the laboratory tests. In addition, Hunt-Hess scales [14] and World Federation of Neurosurgery Societies (WFNS) [15] grade were used to assess the severity of clinical symptoms. Modified Fisher score [16] was employed to evaluate the degree of CV. Assessment of functional independence was performed by the Modified Rankin Scale (mRS) [17]. All clinical baseline data were conducted upon admission and during hospitalization by two researchers who were unaware of the group assignment.

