### Primary and secondary outcomes

The primary outcome was the incidence of CV, while secondary outcomes included the incidence of bleeding events, ischemic events, HIT, deep vein thrombosis, cerebral venous circulation time, brain edema score, and incidence of hydrocephalus. The time points for the primary outcomes are the first and second weeks following the patient’s hospitalization and intervention treatment. The time points.for the secondary outcomes include the first 3 days after hospitalization, the first and second weeks, and the follow-up within 1 year after discharge. The CV was defined as the presence of significant neurological deficits in patients, with TCD ultrasound assess a mean flow velocity of the middle cerebral artery (MCA) exceeding 120 cm/s or a Lindegaard ratio (mean flow velocity of MCA/mean flow velocity of extracranial internal carotid artery) greater than 6. Computed tomography angiography scans showed temporary narrowing of cerebral artery. Regardless of the severity or clinical status of the patient, it was evaluated as CV.

Bleeding events are defined as bleeding that occurs in any part of the body, including intracerebral hemorrhage, gastrointestinal bleeding, and subcutaneous bleeding. According to the standardized bleeding score of Bleeding Academic Research Consortium (BARC), it has 5 types [18]. Type 1 refers to bleeding that is considered insignificant and does not prompt the patient to seek medical attention. Type 2 bleeding includes any obvious sign of hemorrhage that requires medical attention, diagnostic testing, hospitalization, or treatment by a healthcare professional. Type 3 bleeding encompasses clinical, laboratory, and/or imaging evidence of bleeding that requires a specific response from a healthcare provider. Type 4 bleeding is related to coronary artery bypass grafting within 48 h, and type 5 bleeding is fatal. Fatal bleeding can be categorized as intracranial, gastrointestinal, retroperitoneal, pulmonary, pericardial, genitourinary, or other.

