Ischemic events include cerebral and cardiac ischemia, with cerebral ischemia encompassing transient ischemic attacks and stroke, while cardiac ischemia includes angina pectoris and myocardial infarction. HIT is defined as a decrease in platelet count of 50% or more after the therapy of heparin. Deep venous thrombosis includes lower limb deep venous thrombosis and pulmonary embolism, which is diagnosed by a respiratory physician based on pulmonary vascular examination and blood D-dimer testing. The diagnose of lower limb deep venous thrombosis is detected by ultrasound. Hydrocephalus is defined as an enlargement of the cerebral ventricles as visualized on a brain CT scan.

Cerebral venous circulation time is defined as the time required for blood to enter the venous sinus through the deep and superficial veins of the brain and then be drained into the jugular vein, including microvascular cerebral circulation time, venous cerebral circulation time, and the PRECISE score. Following S. Wang’s research, the starting point T1 is set as the first image in the sagittal view of digital subtraction angiography (DSA), which depicts the contrast dye within the branches of the middle cerebral cortical arteries [19]. The vein image that shows the peak filling of the parietal cortical vein is set as T2, and the only disappearance of the sigmoid sinus was set as T3. The mCCT is expressed as T2-T1, while vCCT is expressed as T3-T2.

The PRECISE score is based on the venous filling level shown on the head CTA. A score of 2 represents complete filling that is consistent with the degree of filling in the contralateral hemisphere, while a score of 1 represents partial filling, and a score of 0 indicates no filling. The filling difference of the affected hemisphere veins is calculated based on the PRECISE score. A higher score indicates the improved cerebral venous outflow, while a lower score signifies the decreased cerebral venous outflow. A score of 2 will be given for “complete” contrast filling of the opposite hemisphere, while a score of 1 will be given for “partial” (moderate contrast filling). The PRECISE score will be calculated using the composite score of the normal hemisphere SMCV + VOT + VOL + BVR minus the composite score of the lesioned hemisphere SMCV + VOT + VOL + BVR [20].

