The assessment of brain edema is mainly based on SEBES score which is mainly based on head CT images and intracranial pressure monitoring values during hospitalization [21]. Head CT scans will be conducted at four stages: at the time of admission (0–2 days after aSAH), after endovascular treatment (4–7 days after aSAH), during hospitalization (7–14 days after aSAH), and before discharge (14–21 days after aSAH). Two blinded neurologists specializing in cerebrovascular diseases will independently evaluate the SEBES value of the patients. The scoring criteria will range from 0 to 4 points. Two pre-determined levels in each hemisphere will be defined, and 1 point will be given for visible sulcal effacement due to the interruption of the gray-white matter connection. Intracranial pressure monitoring will include intracranial ICP monitoring, which is recorded by placing an intracranial probe.

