### Statistical analyses

The data analysis will be carried out with statistical software (SPSS, version 26, SPSS Inc). The covariates between groups will be balanced based on Propensity score matching (PSM). The results of outcomes will be analyzed for differences between the UFH group and LMWH group, using the Student *t*-test, chi-square test, and Mann–Whitney *U* test. For continuous variables, the normality test is estimated using the mean (standard deviation). If parameters are not normally distributed, their median (interquartile range) will be reported. For categorical variables, the proportions of the two groups will be presented. Spearman’s correlation analysis is performed on nonnormal continuous variables. Pearson’s correlation is employed for categorical variables. Variables with differences between the two groups will be analyzed by univariate analysis and multifactor logistic regression. Cox multivariate regression analysis will be used for time-to-events data. All statistical tests are two-sided with *p* < 0.05, crude odds ratio (OR), and confidence intervals (CI) will be calculated. In addition, the number of recruitments, participants lost due to follow-up, violations of the protocols, and other relevant descriptive data will be reported. The missing data will be handled using multiple imputation methodology.

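### Hydrocephalus is called an incidence but defined as any ventricular enlargement on CT, so enlargement that predates treatment can count and pull the ratio between arms toward 1

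*Protocol article*

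**What the plan says.** All places are in the protocol article.

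- **Primary and secondary outcomes.** The list of secondary outcomes ends with "brain edema score, and incidence of hydrocephalus". The definition is "Hydrocephalus is defined as an enlargement of the cerebral ventricles as visualized on a brain CT scan". It names no reference scan and does not ask that the enlargement be new or larger than before. On timing, the section says that the time points for "secondary outcomes include the first 3 days after hospitalization, the first and second weeks, and the follow-up within 1 year after discharge".
- **Inclusion and exclusion criteria.** Patients may be admitted up to 72 h after symptom onset. Hydrocephalus already present is not an exclusion.
- **Baseline assessment.** The list runs from demographics to "surgical intervention (e.g., decompressive craniectomy), and results of the laboratory tests", followed by clinical grading scales. Neither hydrocephalus nor ventricular size is named.
- **CT schedule.** For the brain edema score, scans are planned in four stages, the first "at the time of admission (0–2 days after aSAH"). The Interventions section adds that "a weekly follow-up head CT will be performed". Neither place ties a scan to the hydrocephalus definition.
- **Start of treatment.** "The UFH group will start intravenous infusion of UFH 24 h after the embolization procedure", after a head CT that checks for bleeding.
- **Statistical analyses.** "The results of outcomes will be analyzed for differences between the UFH group and LMWH group". The section gives no restriction to patients free of hydrocephalus at entry.

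**The concern.** An incidence counts new cases, whereas the stated rule describes a state. A patient whose ventricles were already enlarged by the bleed on the admission CT, and are still enlarged a week later, satisfies the rule although nothing new has happened. The early time point makes this more likely, because a scan in the first 3 days of hospitalization may have been taken before any study drug.

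The article does write a change-based rule elsewhere in the same section: heparin-induced thrombocytopenia is a fall in platelets of at least half following heparin. Hydrocephalus has no such anchor. So the issue is what the stated rule counts, and not merely a detail left to a fuller document.

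At stake are the interpretability of a reported hydrocephalus rate and the ability of that comparison to show a difference. Cases present at entry add the same expected share to both arms. They also add noise, since a chance imbalance at entry carries straight into the outcome.

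**Working it through.** **The plan's own figure.** There is none for hydrocephalus. The sample size section sizes vasospasm only, at 228 per group with 10% dropout. That is used here just to obtain an evaluable number: 228 × 0.9 = 205.2, taken as 205 per arm. (The randomization section gives 143 per group. This would lower every power figure below but leave the ratios unchanged.)

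**Assumed inputs, not in the documents**
- New-case risk in patients without hydrocephalus at entry: 10% with UFH, 20% with LMWH (true RR 0.50).
- b, the share with enlarged ventricles at entry that are still enlarged on a counted scan: 10% to 40%, equal in expectation in both arms.
- Worsening in patients already affected at entry is ignored.

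**Formulas**
- Literal rule: risk = b + (1 − b) × p.
- New cases only, all randomised in the denominator: risk = (1 − b) × p.
- SE = √[(r₁(1 − r₁) + r₂(1 − r₂)) / 205]; power = Φ(|r₁ − r₂| / SE − 1.96), two-sided 0.05.

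**Worked case, b = 20%**
- Literal: LMWH 0.20 + 0.80 × 0.20 = 0.36; UFH 0.20 + 0.80 × 0.10 = 0.28. Difference 0.08. RR = 0.28 / 0.36 = 0.78. OR = (0.28/0.72) / (0.36/0.64) = 0.69. SE = √[(0.2304 + 0.2016) / 205] = 0.0459. Power = Φ(1.74 − 1.96) = 41%.
- New cases: 0.16 v 0.08. Difference again 0.08. RR 0.50. OR = (0.08/0.92) / (0.16/0.84) = 0.46. SE = √[(0.1344 + 0.0736) / 205] = 0.0319. Power = Φ(2.51 − 1.96) = 71%.

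**Range**

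| b | Literal risks, LMWH v UFH | Difference, both rules | Literal RR | Literal OR | Power, literal | Power, new cases |
|---|---|---|---|---|---|---|
| 10% | 28% v 19% | 9 points | 0.68 | 0.60 | 58% | 77% |
| 20% | 36% v 28% | 8 points | 0.78 | 0.69 | 41% | 71% |
| 30% | 44% v 37% | 7 points | 0.84 | 0.75 | 30% | 64% |
| 40% | 52% v 46% | 6 points | 0.88 | 0.79 | 23% | 57% |

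A pooled-variance test changes the powers by at most about one point.

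**Share of counted outcomes present at entry.** This is 2b / (sum of the two literal risks): 0.20 / 0.47 = 43% at b = 10%, and 0.80 / 0.98 = 82% at b = 40%.

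**Chance imbalance.** At b = 20% the between-arm difference in entry hydrocephalus has SE √(2 × 0.2 × 0.8 / 205) = 0.0395, about 4 points, against an 8-point treatment difference.

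**Other assumed risks.** With new-case risks of 20% v 30% (true RR 0.67), the literal RR is 0.28 / 0.37 = 0.76 at b = 10% and 0.44 / 0.51 = 0.86 at b = 30%.

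**What does not depend on the assumed rates.** Adding the same b to both arms gives a difference of (1 − b)(p₁ − p₂), exactly what new-case counting over all randomised patients gives. Where UFH and LMWH differ, the ratio moves toward 1. In the cases tabulated the SE also rises.

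**The case against.** The strongest reply is that this is a condensed article. The word incidence normally means new cases, and an enlargement can itself be read as a change. The reference scan may be fixed in the full protocol. This stands in part: the intended rule may well be new onset. But the article does state a definition, and nothing in it, in the eligibility criteria or in the baseline list enforces that reading.

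Second, every rate in the illustration is assumed, and the trial claims no power for hydrocephalus. That stands in full. The table shows how the effect works and does not estimate its size in this trial.

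Third, the Statistical analyses section plans covariate balancing and multivariable logistic regression for variables that differ between groups, which could absorb an imbalance at entry. The cover is partial, because entry hydrocephalus is not named among the variables to be collected.

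Three stronger readings are tempting and are not supported:
- A reader might infer that one enlargement is counted afresh on every later scan. The article does not say how repeat scans are combined, and persistence is needed for it to count later at all.
- A reader might infer a bias toward one drug. Randomization makes the added share equal in expectation, and the risk difference over all randomised patients is unaffected.
- A reader might infer that enlargement present at entry can carry no information on heparin. Treatment could affect whether it persists or resolves. Presence at a time point is a legitimate outcome, but it is not an incidence.

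**Conclusion.** The point holds as a minor one. The stated definition does not measure the incidence it is meant to measure, and followed literally it admits cases that predate treatment. The consequence is an odds or risk ratio closer to 1 and a noisier comparison, in both arms alike. The odds ratio matters because it is the effect measure the Statistical analyses section names.

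The size cannot be fixed from the documents. Under the assumptions shown, a true RR of 0.50 would appear as 0.68 to 0.88, with power of 58% down to 23% against about 77% down to 57% for new-case counting. If only part of the entry enlargement persists to a counted scan, b and the dilution shrink accordingly. One of seven secondary outcomes is affected. The primary outcome and the sample size are not.

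**What to change.** Define the outcome as new or increased ventricular enlargement, seen after the start of study treatment, compared with the admission CT. Use that same reference scan in both arms, with readers blinded to allocation. Record hydrocephalus on the admission CT as a baseline variable and adjust for it.

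Two alternatives are weaker:
- Taking the last scan before the first dose as the reference could make it later in one arm, because the Interventions section describes a pre-dose CT only for the UFH group.
- Adding drainage or a shunt as an outcome criterion would tie the outcome to a treatment decision open to knowledge of allocation, in a trial that the abstract calls open-label and the Study design section calls double-blind.

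The definition should refer to the admission scan itself. Its label of days 0–2 does not cover everyone who may enter up to 72 h after onset.

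Cost: protocol wording, one baseline item, and a ventricular reading of CTs that are already scheduled, compared side by side. No extra scans are needed. The downside is fewer counted events. Enlargement that develops between the admission CT and the first dose would still count in both arms if it persists, so some dilution remains.

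### The PRECISE score names both a vein filling grade and a between-hemisphere difference, and the one stated direction is reversed for the difference

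*Protocol article*

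**What the plan says.** All of the relevant text is in the Protocol article, Primary and secondary outcomes, where cerebral venous circulation time is defined.

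- **Place in the outcome set.** Cerebral venous circulation time is a secondary outcome with three parts: "including microvascular cerebral circulation time, venous cerebral circulation time, and the PRECISE score".
- **Grade for a vein.** "A score of 2 represents complete filling that is consistent with the degree of filling in the contralateral hemisphere". Veins that fill only in part are graded 1, and those that do not fill are graded 0.
- **Link to a difference.** "The filling difference of the affected hemisphere veins is calculated based on the PRECISE score".
- **Direction.** "A higher score indicates the improved cerebral venous outflow, while a lower score signifies the decreased cerebral venous outflow".
- **Formula.** The last sentence of the paragraph says that the PRECISE score will be the composite for the "normal hemisphere SMCV + VOT + VOL + BVR minus the composite score of the lesioned hemisphere SMCV + VOT + VOL + BVR".

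The article gives no other direction for the PRECISE score. The Statistical analyses section adds only that tests are two-sided at the 5% level.

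**The concern.** The formula and the direction sentence cannot both be right for the same quantity. The lesioned hemisphere is the term subtracted ("minus the composite score of the lesioned hemisphere"), so better filling there makes the result smaller, yet the article reads a smaller result as worse outflow.

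At stake is which arm is described as having the better venous outflow. The closing paragraphs of the Discussion list cerebral venous circulation among the effects to be analysed, beside vasospasm and brain edema, and say that the effect of heparin on it in this disease is unstudied. By the article's own account, then, no earlier result in this setting would make a reversed one look odd. A two-sided test gives no warning either, because its p-value is the same whichever way the score is signed.

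**Working it through.** The article gives no numerical value for this score, so there is no figure to reproduce. The check is to work through the stated scale.

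**Inputs, all from Primary and secondary outcomes**

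- Four veins per hemisphere: SMCV, VOT, VOL and BVR.
- Each vein graded 0 (none), 1 (partial) or 2 (complete).
- PRECISE score P = N − L, where N is the normal-side composite and L the lesioned-side composite.

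**Step 1: range.** Each composite runs from 4 × 0 = 0 to 4 × 2 = 8. In principle P therefore runs from 0 − 8 = −8 to 8 − 0 = +8.

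**Step 2: direction.** Hold N fixed and raise L by one point: N − (L + 1) = P − 1. Each point of better lesioned-side filling lowers P by 1. This is true at every value of N.

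**Step 3: the case where the normal side fills fully (N = 8).**

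| Lesioned composite L | P = 8 − L | Actual lesioned-side filling | Reading under the stated direction |
|---|---|---|---|
| 8 | 0 | best | worst |
| 6 | 2 | | |
| 4 | 4 | | |
| 2 | 6 | | |
| 0 | 8 | worst | best |

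**Step 4: what an arm comparison would show.** The per-vein probabilities here are assumed purely for illustration, with N = 8 in both arms.

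- Arm A, probabilities of grades 0/1/2 = 0.1/0.3/0.6: mean L = 4 × (0.3 × 1 + 0.6 × 2) = 4 × 1.5 = 6.0, so mean P = 8 − 6.0 = 2.0.
- Arm B, probabilities 0.2/0.4/0.4: mean L = 4 × (0.4 × 1 + 0.4 × 2) = 4 × 1.2 = 4.8, so mean P = 8 − 4.8 = 3.2.

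Arm A has the better filling and the lower P. Under the stated direction, Arm B (3.2) would be called improved relative to Arm A (2.0).

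**Step 5: effect on the test.** Replacing P by −P changes the sign of the between-arm difference and nothing else. "All statistical tests are two-sided with" a 5% threshold, so the p-value is the same under either sign; only the arm named as better changes.

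**Step 6: the same direction applied to the vein grade.** For a single vein, 2 is complete filling and 0 is none, so higher is better and the direction sentence is correct. It fails only when carried over to the difference, which bears the same name.

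**The case against.** The strongest counter-argument is that the paragraph can be read coherently. It uses the word score first for the 0-2 filling grade. The direction sentence is followed at once by another description of that grade, and the subtraction comes only at the end. The sentence on the filling difference can also be taken to mean that the PRECISE score is an input to the difference rather than the difference itself. On that reading, higher is better is a true statement about the grade.

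Part of this stands. The direction is right for the grade, so the fault may be one name for two quantities rather than a wrong direction as such. It does not clear the text, because the final sentence calls the difference the PRECISE score, that is the only calculation given for the outcome, and no other direction is stated for it.

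A reader might go further and infer that any significant venous result is bound to be credited to the wrong arm. The documents do not support that. The error arises only if both sentences are applied literally to the difference; an analyst who reports vein filling directly, or notices the conflict, would avoid it. A reader might also infer that 0 is always the best state and 8 the worst. That assumes full filling on the normal side: 0 also results when neither side fills (0 − 0 = 0). The difference measures the lesioned side relative to the normal side, not outflow overall.

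Nor do the documents show that the direction sentence, rather than the order of subtraction, is the slip. The scale is taken from a cited source that is not available here.

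**Conclusion.** The point holds as an inconsistency in an outcome definition. One name covers a grade for which higher is better and a difference for which, at fixed normal-side filling, higher is worse by exactly one point per point of lesioned-side filling. That relation rests only on the stated formula; the 0-to-8 range additionally assumes full normal-side filling.

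The consequence is conditional: if the stated direction is applied to the calculated score, the arm with poorer lesioned-side filling would be reported as improved. It touches one of three components of one of seven secondary outcomes. The microvascular and venous circulation times, the p-value, the sample size and the primary outcome are not affected. It should be corrected, but it does not threaten the trial's main conclusion.

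**What to change.** Before analysis, check the cited scale and make the formula and the direction agree in one of two ways:

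1. Keep normal minus lesioned, and state that a lower difference means better lesioned-side outflow relative to the normal side.
2. Reverse the subtraction to lesioned minus normal, and keep higher as better. With the normal side full, the score then runs from −8 (no lesioned-side filling) to 0 (lesioned side also full).

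In either case, call the 0-2 rating the vein filling grade, so that PRECISE score means only the composite difference.

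The cost is a few sentences of text, with no change to imaging, data collection or design. Settling the sign before results are seen also removes any room to choose it afterwards.

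### The PRECISE score is defined as a difference between hemispheres, so it measures asymmetry of venous filling and not the level of outflow that the protocol says it reflects

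*Protocol article*

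**What the plan says.** All of this is in the protocol article under Primary and secondary outcomes.

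- **Role.** Cerebral venous circulation time is a secondary outcome: "secondary outcomes included the incidence of bleeding events, ischemic events, HIT, deep vein thrombosis, cerebral venous circulation time, brain edema score". It has three parts, "including microvascular cerebral circulation time, venous cerebral circulation time, and the PRECISE score".
- **Vein grades on CT angiography.** "A score of 2 represents complete filling that is consistent with the degree of filling in the contralateral hemisphere"; "a score of 1 represents partial filling, and a score of 0 indicates no filling".
- **Formula.** PRECISE is the "composite score of the normal hemisphere SMCV + VOT + VOL + BVR minus the composite score of the lesioned hemisphere SMCV + VOT + VOL + BVR".
- **Direction.** "A higher score indicates the improved cerebral venous outflow, while a lower score signifies the decreased cerebral venous outflow".
- **The two timing components**, read from DSA: "The mCCT is expressed as T2-T1, while vCCT is expressed as T3-T2".
- **Brain edema (SEBES)** is scored on both sides: "Two pre-determined levels in each hemisphere will be defined".

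**The concern.** The text gives the score a meaning, level of venous outflow, that the formula does not deliver. Subtracting one side from the other keeps only the imbalance. A patient with no filling on either side gets the same value as a patient with full filling on both.

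This matters in this trial for three reasons. The disease is subarachnoid hemorrhage, and the protocol itself scores its edema in each hemisphere, so two-sided involvement is expected. Both study drugs act systemically, so a change on both sides is a natural effect to look for. The Discussion also names cerebral venous circulation as something on which the two drugs will be compared. To the extent that a difference between arms is common to both sides, this component would tend to understate it.

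The definition of grade 2 adds to the problem. Because complete filling is tied to the opposite side, two equally poorly filled hemispheres could each be graded as complete. Bilateral impairment would then be lost before any subtraction.

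**Working it through.** The plan states no numerical result for PRECISE, so there is no figure to reproduce. The check applies the formula directly and then simulates it.

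**Step 1: range.** Four veins × grades 0–2 give N (normal side) and L (lesioned side) from 0 to 8. D = N − L runs from −8 to +8. The sum S = N + L runs from 0 to 16.

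**Step 2: equal filling.**
- 8/8: D = 0, S = 16
- 4/4: D = 0, S = 8
- 0/0: D = 0, S = 0

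All nine symmetric states give D = 0.

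**Step 3: the same gain of 2 on both sides, each side capped at 8.**
- 4/2 → 6/4: D stays at 2
- 5/5 → 7/7: D stays at 0
- 8/4 → 8/6: D falls from 4 to 2
- 8/6 → 8/8: D falls from 2 to 0

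So the effect cancels when both composites can move equally, and it shows when the normal side is at its ceiling. Take all states with L ≤ N except 8/8, and gains of 1 to 8 on both sides: D changes in 204 of 352 cases. This is a count of cases, not a probability.

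**Step 4: direction.** 8/8 gives 0, 8/4 gives +4 and 8/0 gives +8. The worst lesioned side has the highest score, although the text calls higher better. In Step 3 the visible benefit appears as a fall in D, which the stated direction would read as worse outflow.

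**Step 5: size under assumptions.** The Sample size estimation section gives 228 per group and 10% dropout: 228 × 0.9 = 205 evaluable per arm. (The Randomization and blinding section gives 143 per group; the larger figure is used here.) The following are assumptions and are not in the document:
- latent normal filling, cut at −1 and 0.3 into grades 0, 1 and 2
- within-patient correlation 0.3–0.7
- a treatment shift of 0.3 latent SD on both sides
- side asymmetry as shown in the table

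The test is the Mann–Whitney U test, which the Statistical analyses section names, two-sided at 0.05, with 600 simulated trials per setting.

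| Asymmetry between sides (latent SD) | Rejection by difference D |
|---|---|
| 0 | 4–6% |
| 0.3 | up to about 10% |
| 1.0 | 58–65% |
| 1.5 | 79–91% |
| 2.0 | 85–97% |
| 3.0 | 90–99% |

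The bilateral sum rejects in about 90–99% throughout (88–99% at 2.0 SD, 91–99% at 3.0 SD). At zero asymmetry the mean of D does not move, while the sum moves by about 1.4 points.

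**Step 6: the reverse case.** If the same shift acts on the lesioned side only and asymmetry is low, the difference rejects in about 99–100% and the sum in about 37–60%. Neither summary is better in every case.

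**The case against.** A reader might infer that a drug effect on both sides cannot be seen at all. The documents do not support that. The formula presupposes a normal hemisphere, and such a side may sit at or near 8. A bilateral benefit then raises mainly the lesioned side, and D moves. With marked asymmetry the difference loses little power against the sum, as Step 5 shows. The document gives no data on venous asymmetry in these patients, so the low rejection figures describe only near-symmetric disease. This objection stands and limits the claim.

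A reader might also infer that a bilateral effect would be lost to the trial. It would not: the two DSA timing measures in the same outcome are elapsed times with no subtraction between sides.

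PRECISE is also taken from a cited source that is not shown, and a sum over both sides is not that published score. This stands as a reason to keep the difference and report it under its own name. It does not make a difference score measure level of outflow.

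Finally, one could fault the article for giving no rule on which hemisphere counts as lesioned in midline or two-sided disease. A condensed article may leave that to the full protocol or a reading manual, and it does not say how many aneurysms are midline. It is not counted as a defect here. It matters for the fix, because swapping sides reverses the sign of D.

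**Conclusion.** The concern holds in a limited form. As written, PRECISE measures side-to-side asymmetry, while the text presents it as a measure of how good venous outflow is. Equal filling at any level scores 0, equal changes on both sides cancel, and the grade 2 definition can hide bilateral impairment further. The stated direction also contradicts the formula.

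The first three of these, and the contradiction in direction, follow from the text alone. The size of the loss does not. Under the assumed settings, power of the difference for a two-sided shift runs from about 5%, no better than chance, to over 85%, depending on an asymmetry that the document does not give. The documents therefore do not support saying that a real difference between arms would in general be reported as no effect. The limit touches one of three components of a secondary outcome and leaves the primary outcome unaffected. It is worth correcting before the CT angiograms are scored.

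**What to change.** 1. Grade each vein on its own filling (2 complete, 1 partial, 0 none), without reference to the opposite side. Without this step the sum would inherit the same blind spot.
2. Compare between arms the sum over both hemispheres (0–16, higher = better outflow) as the measure of venous outflow.
3. Report the cited normal-minus-lesioned difference alongside it, under its own name, as a measure of asymmetry. Reconcile its stated direction with the formula, and fix the lesioned side before allocation is known.

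The same CT angiography readings serve both summaries, so no new procedure is needed. The cost is a change to the outcome definition and the grading instruction. The downside is that the sum is not the published score, and it is less sensitive than the difference when an effect is confined to the lesioned side. Both should therefore be shown.
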